## Abstract

**Background:**

Recent advances in the field of congenital heart disease (CHD) led to an improved prognosis of the patients and in consequence the growth of a new population: the grown up with congenital heart disease. Until recently, more than 50% of these patients were lost to follow up because of the lack of specialized structures. The critical moment is the transition between paediatric and adult unit. Therapeutic education is crucial to solve this issue by helping patients to become independent and responsible. The TRANSITION-CHD randomized trial aims to assess the impact of a transition education program on health-related quality of life (HRQoL) of adolescents and young adults with CHD.

**Methods:**

Multicentre, randomised, controlled, parallel arm study in CHD patients aged from 13 to 25 years old. Patients will be randomised into 2 groups (education program vs. no intervention). The primary outcome is the change in self-reported HRQoL between baseline and 12-month follow-up. A total of 100 patients in each group is required to observe a significant increase of the overall HRQoL score of 7 ± 13.5 points (on 100) with a power of 80% and an alpha risk of 5%. The secondary outcomes are: clinical outcomes, cardiopulmonary exercise test parameters (peak VO2, VAT, VE/VCO2 slope), level of knowledge of the disease using the Leuven knowledge questionnaire for CHD, physical and psychological status.

**Discussion:**

As the current research is opening on patient related outcomes, and as the level of proof in therapeutic education is still low, we sought to assess the efficacy of a therapeutic education program on HRQoL of CHD patients with a randomized trial.

***Trial registration*:**

This study was approved by the National Ethics Committee (South-Mediterranean IV 2016-A01681-50) and was registered on Clinicaltrials.gov (NCT03005626).

## Background

Congenital heart diseases (CHD) are the first cause of congenital abnormality at birth. As a result of significant improvements in surgical techniques and intensive care, more adults than children are currently living with a CHD [1–4]. However, young patients with a CHD are prone to interrupt their follow-up soon after transfer from paediatric to adult cardiology and are therefore at risk to reintegrate the healthcare system when facing a complication [5, 6]. Indeed, more than 30% of adults with a CHD are lost to follow-up despite a significant risk of arrhythmia, heart failure, pulmonary hypertension and acquired cardiovascular diseases [7, 8]. Even patients with lower-complexity CHD are concerned with a higher burden of adverse cardiovascular events relative to the general population [7]. Some lost to follow-up adult patients with a CHD reintegrate the healthcare system for administrative issues: they may be referred to an expert CHD centre by an occupational medicine physician, or when taking out a bank loan by an insurance service. Lost to follow-up female CHD patients are frequently referred by obstetricians in early pregnancy.

This public health issue has been integrated in the recent European and American CHD guidelines, which emphasized the interest of structured transition education programs dedicated to adolescents and young adults with CHD, before transfer to adult care [9, 10]. Transition education programs intend to improve patients’ knowledge of their medical condition, and answer their questions about physical activity, sexuality, graduate studies, and professional carriers [6, 11]. Those programs aim to promote patient autonomy in order to limit loss to follow-up, and, ultimately, improve medical care.

Various transition education programs have being experimented worldwide in patients with CHD, however, their real impact on patient care has been scarcely evaluated [5, 6, 11–13]. Heterogeneity in terms of type of education, disease severity and patient demographic characteristics may result in biased interpretation on the actual program’s efficacy. Moreover, patient reported outcomes assessment such as health-related quality of life (HRQoL), and qualitative analyses, should be part of such education programs’ evaluation [14–18].

Most importantly, randomised controlled trials are necessary to increase the level of evidence in the field of CHD patient education [19, 20].

In a pilot study evaluating the implementation of our own transition program, we showed that patients with complex CHD, poor disease knowledge, risk behaviours, and lower age, were more likely to join this transition program [6]. However, these preliminary results come from a non-randomized controlled study. Therefore, the impact of this transition program needs to be determined with a higher level of evidence.

In the TRANSITION-CHD trial, we aim to assess the impact of a non-selective structured education transition program on HRQoL of adolescents and young adults with CHD, through a regional multicentre randomised trial. We also intend to perform a qualitative phenomenological study to explore how these young patients experience the TRANSITION-CHD program and identify key factors for success or failure.

## Methods

### Study design

The TRANSITION-CHD trial is an open label prospective, multicentre, randomised, controlled, parallel arm study. Patients will be followed for 12 months with an expected recruitment time period of 24 months.

Once the informed consent will be given, participants will be randomly allocated in a 1:1 ratio to either intervention (e.g. transition education program) or control group arms. In the control group, patients will have a regular non-modified follow-up with no formalized transition education program during the 12-month study period. However, they will be offered to participate in the transition therapeutic education program, once the 12-month study period is over (Fig. 1).

**Fig. 1 Fig1:**
[figure not shown]
Flow chart

Randomisation will be stratified by age group (13–17 years and 18–25 years), centralised, using a secure, web-based randomisation system (Ennov Clinical Software) managed by the Clinical Research Unit of Montpellier University Hospital, independently from the investigators.

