### Setting

Overall, 3 CHD centres in the south of France will participate in the study (Montpellier University Hospital, Saint-Pierre Institute, Toulouse University Hospital). A total of 17 investigators will oversee patient recruitment. These investigators are cardiac surgeon (n = 1), paediatric cardiologists (n = 11), adult congenital cardiologists (n = 2) or both (n = 3). Patients will be recruited in tertiary care centres labelled by health authorities as referral centres for complex congenital heart diseases (e.g. “M3C” national health network).

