### Main outcome

The main outcome is the change between baseline (M0) and 12-month follow-up (M12) of the PedsQL self-reported HRQoL score. The PedsQL generic HRQoL questionnaire has four multidimensional scales: physical functioning (8 items), emotional functioning (5 items), social functioning (5 items), and school functioning (5 items). The three summary scores are: total scale score (23 items), physical health summary score (8 items) and psychosocial health summary score (15 items). Each item uses a 5-point Likert scale from 0 (never) to 4 (almost always). Items are reversed scored and linearly transformed to a 0–100 scale, higher scores indicating a better HRQoL. Psychometric properties showed reliability, validity and responsiveness to clinical change over time [22]. After translation and cultural adaptation, the psychometric properties of the French version of the PedsQL appeared to be acceptable [23]. Two versions of the PedsQL questionnaire (13–17 and 18–25 years old) will be used for adolescents and young adults, respectively.

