## Discussion

In the continuity of our clinical research program on HRQoL in patients with CHD [6, 14, 30–32, 34], we expect to observe an improvement of HRQoL in patients undergoing the transition education program. Patient-reported outcomes (PRO) have been increasingly used in clinical research [35], therefore, using HRQoL as a primary outcome in the TRANSITION-CHD trial seems particularly adapted to such a therapeutic education program. Indeed, as defined by the World Health Organization, “therapeutic education should try to give and maintain the necessary competences to handle chronic disease with the objective of improving patient HRQoL”.

Currently, the level of evidence of research in therapeutic education needs to be improved, despite all methodological constraints and biases inherent to qualitative research: various qualitative outcomes, heterogeneous educational content, ethical issues related to randomisation, program based on voluntary patient participation, etc. [36]. The TRANSITION-CHD trial will use several quantitative instruments assessing various aspects of the patient well-being: self and proxy-reported HRQoL, anxiety, depression, level of autonomy and disease knowledge. In order to limit the level of content heterogeneity, this education program is based on a single and joint structure between all tertiary care CHD centres from the same region [6]. Therefore, ethical issues have been considered in the study design, and patients randomised in the control group will be offered to participate in the transition program, without any additional cost, after the 12-month study period. Since the creation of the program in 2015, all paediatric and adult congenital cardiologists from the regional M3C network have been particularly motivated to enrol their patients and participate themselves in the education sessions. Active support from all patient organisations has played an important role in promoting the program, as shown in several videos dedicated to young patients with CHD (https://www.youtube.com/watch?v=OJ67oIm0Wv8).

Promotion of physical activity is a major educational objective of the transition program. Indeed, exercise capacity in the CHD population may be impaired and many adolescents with a sedentary lifestyle are trapped in the vicious circle of physical deconditioning [15, 24, 31, 34]. Similar therapeutic education messages focusing of sports participation have been integrated into cardiac rehabilitation programs [15].

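### Randomisation is stratified by age group only and the stated primary test has no centre term, so a three-centre trial gives up a little precision that a prespecified adjustment would recover.

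*Protocol article*

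**What the plan says.** The randomisation paragraph under Methods, Study design, reads "Randomisation will be stratified by age group" (13–17 and 18–25 years), and goes on to describe a centralised, web-based system run independently of the investigators. No other stratification factor is named. Study design also states that "participants will be randomly allocated in a 1:1 ratio".

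Under Setting: "Overall, 3 CHD centres in the south of France will participate in the study", with 17 investigators. The expected share of patients per centre is not given.

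On the comparator, Study design says "patients will have a regular non-modified follow-up with no formalized transition education program during the 12-month study period". On the intervention, the Discussion says that "this education program is based on a single and joint structure between all tertiary care CHD centres from the same region".

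For the endpoint, "The main outcome is the change between baseline (M0) and 12-month follow-up (M12) of the PedsQL self-reported HRQoL score". Statistical analysis compares this change between arms by a Student or Mann-Whitney test, chosen by distribution. Adjustment or stratification on potential confounders is to be considered in a sensitivity analysis if the groups prove non-comparable.

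**The concern.** In a multicentre trial, centre can stand for case mix, local follow-up practice and staff. The programme is standardised across centres, but the text does not say that the control condition is. The natural reading is that controls continue with whatever follow-up their own centre gives.

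An allocation list that ignores centre lets the arms be uneven within a centre, most easily in a small one. A test without a centre term leaves variation between centres in the error and does not correct the estimate for uneven splits. The planned safeguard depends on the data. If it looks at arm comparability overall, it need not detect uneven splits inside a centre. At stake are some precision in the primary estimate and cleaner within-centre comparisons, which are useful given the authors' hope that similar programmes will be adopted in other regions.

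**Working it through.** **Inputs from the article.** 100 patients per arm; planned difference 7 points; SD 13.5; two-sided alpha 5%; 20% loss, leaving 80 evaluable per arm; 3 centres; 2 age groups.

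**Inputs assumed.** Centre shares of 33/33/33, 50/30/20 or 60/25/15 per cent. Centre means of the change score at −3, 0, +3 (span 6) or −5, 0, +5 (span 10). SD 13.5 taken as the SD within centre. Allocation in blocks of 4 that ignore centre. Age strata were not modelled.

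**1. The plan's own sample size.** n per arm = 2 × (1.96 + 0.842)² × 13.5² / 7² = 58.4, so 59. Dividing by 0.80 gives 74 (75 with the t distribution), not 100. At 90% power the same formula gives 79, or 99 after inflation (80 and 100 with the t distribution). This mismatch is a separate matter. It is relevant here only because baseline power with 80 per arm is about 90.6%, not 80%.

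**2. How uneven a centre can be.** Treating allocation within a centre as Binomial(n, 0.5):

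| Centre size | 95% range in one arm | Chance of 60:40 or worse |
|---|---|---|
| 20 | 6 to 14 | 50% |
| 30 | 10 to 20 | 36% |
| 60 | 22 to 38 | 16% |

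In the simulation with blocks of 4 (4,000 runs per scenario), the 95th percentile of the departure from 50% was about 6 to 17 percentage points, largest in the smallest centre.

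**3. What that does to the estimate.** With 100 per arm, the chance difference between arms in mean centre effect has SD ≈ √(V × 2/100), where V is the variance of the centre effects across patients.

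- Equal shares, span 10: V = (25 + 0 + 25)/3 = 16.67; SD = √0.333 = 0.58; 1.96 × 0.58 = 1.13 points. Simulated: SD 0.57 to 0.58, 95th percentile 1.15.
- Shares 60/25/15, span 6: mean = −1.8 + 0.45 = −1.35; V = 5.4 + 1.35 − 1.35² = 4.93; SD = √0.0986 = 0.31; 1.96 × 0.31 = 0.62 points. Simulated: SD 0.32, 95th percentile 0.60.

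The simulated mean shift was within about 0.01 point of zero in every scenario.

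**4. Type I error.** With centre differences present, the unadjusted test rejected in 4.7% to 5.2% of runs (Monte Carlo standard error √(0.05 × 0.95/4000) = 0.34 percentage points). There is no inflation.

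**5. Power.** Approximate power is Φ(7 / (s × √(2/80)) − 1.96).

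- Centre term in the model, s = 13.5: 7/2.135 = 3.279, power 90.6%.
- No centre term, equal shares, span 10: s = √(182.25 + 16.67) = 14.10; 7/2.230 = 3.139, power 88.1%. Loss 2.5 percentage points.
- No centre term, equal shares, span 6: s = √(182.25 + 6) = 13.72; 7/2.169 = 3.227, power 89.7%. Loss 0.9 percentage points.

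Simulation agrees:

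| Shares, span | No centre term | With centre term |
|---|---|---|
| 33/33/33, 6 | 88.8% | 89.9% |
| 33/33/33, 10 | 87.5% | 90.1% |
| 50/30/20, 6 | 89.7% | 90.4% |
| 50/30/20, 10 | 88.2% | 90.3% |
| 60/25/15, 6 | 89.3% | 89.9% |
| 60/25/15, 10 | 88.8% | 91.0% |

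**6. Which remedy does the work.** With shares 50/30/20 and span 10, centre-stratified allocation removed the imbalance shift entirely. Power was then 88.6% without a centre term and 90.3% with one. Without stratification the figures were 88.2% and 90.3%. The gain in power comes from the analysis term; stratifying alone adds almost none.

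**The case against.** A reader might infer that centre is confounded with the programme, so that centre differences bias the result. The documents do not support this. Individual patients are randomised 1:1 through a central system, so any imbalance within a centre is chance, and the error rate of the test already covers it.

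Other points also limit the concern:

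- The endpoint is a within-patient change, so stable differences between centres largely cancel, though not exactly because of regression to the mean. A span of 6 to 10 points in change scores is therefore generous.
- The article never says that usual care differs by centre, and all patients come from labelled tertiary referral centres.
- The joint programme structure argues against large differences between education teams. Exercise-test procedures are to be harmonised, and they serve secondary outcomes only.
- Nothing says that group sessions are filled within one centre, so difficulty in forming groups of 5 to 8 cannot be claimed.
- Even a 10 versus 20 split in a centre of 30 raises the within-centre standard error by only about 6% over 15 versus 15: √(0.150/0.133) = 1.06.
- In an open-label trial, blocking within centre makes allocation somewhat easier to guess, so few strata is a defensible choice.
- Covariate terms are often left to the analysis plan, which is not shown here.

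Most of this stands and reduces the point to one of precision. The last item does not dispose of it, because the article names the primary test and says when adjustment would be considered. That is a stated choice, and it makes adjustment depend on what the data show.

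**Conclusion.** The point holds as a modest, inexpensive improvement. Age group is the only stated stratification factor, three centres recruit, and the stated primary test has no centre term. The consequences are chance imbalance within centres and a small loss of precision: a shift in the estimate of up to about 0.6 to 1.15 points (95th percentile) and a power loss of about 1 to 2.5 percentage points (0.6 to 2.6 across the simulated scenarios). There is no systematic bias and no inflation of type I error.

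These sizes depend on the assumed centre shares, the assumed 6 to 10 point span in change scores, and SD 13.5 being the within-centre SD. If the centres do not differ in mean change, the shift is zero and the centre term gains nothing.

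**What to change.** In Statistical analysis, define the primary comparison of the PedsQL total-score change as a linear model with treatment arm and prespecified terms for centre and for age group, the stratification factor. This replaces the provision to consider adjustment only after non-comparability is seen. If the full analysis plan already does this, bring the article into line with it. The cost is three degrees of freedom (two for centre, one for age group) out of about 160 evaluable patients.

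If recruitment has not started, also stratify the central randomisation by centre and age group, with block sizes that vary and are not disclosed to investigators. This gives 3 × 2 = 6 strata, about 200/6 = 33 patients each on average. The cost is a new allocation list, a few incomplete blocks, and slightly more predictable allocation within a centre in an open-label trial. If recruitment has started, the analysis term alone is enough.

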### Setting

Overall, 3 CHD centres in the south of France will participate in the study (Montpellier University Hospital, Saint-Pierre Institute, Toulouse University Hospital). A total of 17 investigators will oversee patient recruitment. These investigators are cardiac surgeon (n = 1), paediatric cardiologists (n = 11), adult congenital cardiologists (n = 2) or both (n = 3). Patients will be recruited in tertiary care centres labelled by health authorities as referral centres for complex congenital heart diseases (e.g. “M3C” national health network).

### Study population

Patients with a CHD, as defined by the international ACC-CHD classification, [21] and aged from 13 to 25 years old, will be prospectively recruited in the participating centres, during an outpatient visit. Inclusion and exclusion criteria were listed in Table 1.

**Table 1 Tab1:** Trial entry

*Inclusion criteria*
Male or female aged 13–25 years old
Patients with a congenital heart disease (CHD), as defined by the international ACC-CHD classification
Written informed consent for adult patients, or legal guardians and children’s assent for minors
*Exclusion criteria*
Patients who are unable to understand the study information or unable to complete study procedures
Patients with a severe intellectual disability that does not allow the completion of the quality of life questionnaire
Patient who intends to move to another region with a follow-up in another institution during the 12 month study period
Patients participating in concurrent interventional research which may overburden the patient or confound data collection

### Intervention

As previously described, the structure of our transition program [6] involves all educational objectives described in current guidelines on transition care in patients with CHD [9, 10]. The transition education program is divided into three parts, as follows:*First educational outpatient visit (1 h):* this individual interview with a health educator (e.g. a specialist nurse) aims to determine the patient’s educational objectives and needs.*Group session (1 day):* dedicated to patients and their relatives, this group session with 5 to 8 patients of similar age ranges (13–17 years or 18–25 years) and involves two health educators, one paediatric cardiologist, one adult congenital cardiologist, one psychologist and one patient association delegate. The main goal is to promote patient’s self-efficacy and autonomy. The program of the day is divided into four parts:*Medical aspects:* knowledge of the disease, type of repair, follow-up in adult cardiology, and complications.*“Living with a CHD”:* interactive talkgroup (youth and parents separately) including various education tools and addressing several topics (sports, jobs, studies, sexuality, etc.). For the patients, the main goal is to improve their self-advocacy in deciding to act both independently from parents and medical providers, and in interdependence with them. Specific messages to promote physical activity and limit sedentary lifestyle in patients with CHD are delivered by the educational team. For the parents, the main goal is to identify factors that could promote or inhibit their child’s autonomy.*Administrative workshop:* group session (patients and relatives together) addressing various following topics such as social security, insurance or bank loans.*Synthesis and individual interview*: individual interview with a cardiologist and a health educator, to establish a personalized educational report. When needed, additional healthcare and educational objectives are defined, such as psychological support, knowledge reinforcement, cardiac rehabilitation, etc.*Transfer preparation outpatient visit*: approximately 6 months after the group session, the patient undergo a medical visit with both a paediatric cardiologist and an adult congenital cardiologist, to provide an individual feedback from the group session and to prepare the transfer in the adult care CHD centre.

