### Statistical analysis

All included subjects will be considered in the description of the population. An intention-to-treat analysis will be used, and each randomized subject will be analysed in his/her treatment arm. A per-protocol analysis, including all randomized subjects with a valid primary efficacy measurement and with no important protocol deviation (patients who have successfully completed the transition program) that could affect the evaluation of the main outcome, will also be carried out for parameters to assess the impact of the program when compliance is good (> 80% participation in sessions).

A description of the baseline characteristics of each group will be made by giving the frequencies of the different categories for the qualitative variables and the mean with standard deviation or median with interquartile range for continuous variables. In case of non-comparability of the groups, an adjustment or stratification (in case of interaction) on the potential confounding factors will be considered in a sensitivity analysis.

The change in the self-reported HRQoL total score, as well as the changes of the 2 summary and the 4 dimensions scores, will be compared between the two groups using student test or Man-Whitney test, according to the distributions. The effect size will be calculated using Cohen’s d and its 95% confidence limits.

The statistical significance will be set at 0.05 and analyses will be performed using Statistical Analysis Systems version 9 (SAS Institute, Cary, NC, USA).

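### Group sessions of 5 to 8 in the intervention arm only: if 12-month changes correlate within sessions, the named primary test overstates precision and type I error exceeds 5%

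*Protocol article*

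**What the plan says.** Allocation is by patient (Study design): "participants will be randomly allocated in a 1:1 ratio to either intervention (e.g. transition education program) or control group arms". Controls are not grouped: "patients will have a regular non-modified follow-up with no formalized transition education program during the 12-month study period".

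The programme has three parts (Intervention):

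- The first is one-to-one: "this individual interview with a health educator (e.g. a specialist nurse) aims to determine the patient’s educational objectives and needs".
- The second is a one-day session, "this group session with 5 to 8 patients of similar age ranges", led by a multidisciplinary team. It includes discussion among the participants and closes with an individual interview.
- The third is an individual visit about 6 months later, "to provide an individual feedback from the group session and to prepare the transfer in the adult care CHD centre".

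The outcome is a change score (Main outcome): "The main outcome is the change between baseline (M0) and 12-month follow-up (M12) of the PedsQL self-reported HRQoL score". In Statistical analysis, the changes "will be compared between the two groups using student test or Man-Whitney test, according to the distributions", and Cohen's d is to be reported with 95% limits. Neither Sample size nor Statistical analysis mentions session groups, an ICC or a design effect.

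**The concern.** Patients who spend the day in the same session share its discussion, its group dynamics and its staff on that day. Interaction between participants is part of the treatment, and the outcome is self-reported quality of life, which such an experience could move. Outcomes may therefore be alike within a session in the intervention arm, while nothing comparable groups the controls. This is a partially nested design.

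Both named tests treat every patient as an independent observation. Positive correlation within sessions raises the true variance of the intervention mean above what these tests assume. The error runs in one direction, towards too much confidence in the estimated difference. It affects the p-value of the primary comparison and also the confidence limits, which matter even if the programme works.

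This goes beyond a detail left to an analysis plan that is not shown: the article names the primary test, and that test does not match the delivery the article describes.

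**Working it through.** **Inputs from the article.** Group size 5 to 8 (Intervention). Difference 7 points, SD 13.5, two-sided alpha 5%, power 80%, 20% loss or missing data, 100 per arm (Sample size). Evaluable patients: 100 × 0.8 = 80 per arm.

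**Assumed input.** The ICC is not given. The range used is 0 to 0.10.

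**The plan's own figure.** n = 2 × (1.96 + 0.84)² × 13.5² / 7² gives 59 per arm, and 59 / 0.8 gives 74, not 100. At 90% power the same inputs give 79, then 99. So 100 per arm does not follow from the stated 80% but fits 90%. That is a separate matter; here it means that 80 evaluable per arm have about 90.6% power without clustering.

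**Patients per session.** If the 20% loss is spread evenly, 5 × 0.8 = 4 and 8 × 0.8 = 6.4 evaluable patients per session.

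**Formulas for clustering in one arm, equal arms, session size m:**

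- Design effect in the intervention arm: DE = 1 + (m − 1) × ICC. In the control arm it is 1.
- True SE / assumed SE: R = √((1 + DE) / 2).
- Actual two-sided type I error: 2 × (1 − Φ(1.96 / R)).
- Power of a test using the correct SE: Φ(7 / (13.5 × √((1 + DE) / 80)) − 1.96).

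**Example.** m = 6.4, ICC 0.05: DE = 1 + 5.4 × 0.05 = 1.27; R = √1.135 = 1.065; 1.96 / 1.065 = 1.84; type I error 6.6%.

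| ICC (assumed) | R, m = 4 to 6.4 | Type I error, m = 4 to 6.4 | Type I error, m = 5 to 8 (full groups) | Power, m = 4 to 6.4 |
|---|---|---|---|---|
| 0 | 1.000 | 5.0% | 5.0% | 90.6% |
| 0.01 | 1.007-1.013 | 5.2-5.3% | 5.2-5.4% | 90.2-89.9% |
| 0.05 | 1.037-1.065 | 5.9-6.6% | 6.2-7.1% | 88.6-86.8% |
| 0.10 | 1.072-1.127 | 6.8-8.2% | 7.4-9.2% | 86.4-82.9% |

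Coverage of a nominal 95% interval is 100% minus the type I error: for m = 4 to 6.4, about 94.1-93.4% at ICC 0.05 and 93.2-91.8% at ICC 0.10.

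**Check by simulation.** With 80 per arm and sessions of 5 or 8 (30,000 runs each), the t test rejected a true null in 5.1-5.5%, 6.1-7.0% and 7.3-9.2% of runs at ICC 0.01, 0.05 and 0.10, and in 4.9% at ICC 0. The Mann-Whitney test (8,000 runs) was similar, with more simulation noise.

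**Does the sample size suffer?** In the worst case shown (ICC 0.10, evaluable groups of 8), DE = 1.7 and power is 80.6%. For 80% power after 20% loss that case needs 99 per arm, against 100 planned.

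**The case against.** The strongest reply is that the inflation is conditional. It depends on an ICC that the article does not give, and at ICC 0 the tests hold their 5% level. That includes the strict null in which the programme, group interaction included, affects nobody and sessions are not otherwise alike. There are also reasons to expect a small ICC. Only one day is delivered in groups, the other contacts are individual, and the outcome is a generic score at 12 months. Staff may recur across sessions, which would make the team less of a session-level effect. Sessions are formed within the age bands used to stratify randomisation, so likeness due to age band exists in both arms and is not one-arm clustering. If patients outside the trial fill some places, there are fewer trial patients per session and the effect shrinks further.

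All of this stands as a limit on size. None of it shows that the ICC is zero. The strict null also protects only the test: if the programme works and its effect varies between sessions, the unadjusted limits are too narrow.

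A reader might infer more than the article supports, in three ways:

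- That type I error is known to exceed 5%. It is not; that follows only if the within-session correlation is positive.
- That the trial is underpowered for want of a clustering allowance. The figures above show that it is not, for ICCs up to 0.10.
- That a full cluster-trial design effect applies. Patients are randomised individually and only one arm is grouped, so that would overstate the problem.

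**Conclusion.** The point holds in conditional form. The named primary test ignores a grouping that the article itself describes in one arm. If changes correlate within sessions, precision is overstated. The size is modest: an excess in type I error of about 0.2 to 0.3 percentage points at ICC 0.01, 0.9 to 1.6 at 0.05 and 1.8 to 3.2 at 0.10. The highest figure, 9.2%, needs an ICC of 0.10 and every group complete at 8 with no loss, so it is an upper bound rather than an expectation.

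These figures assume equal session sizes, equal total variance in both arms, loss spread evenly over sessions, and every evaluable intervention patient in a session made up of trial patients. The ICC is an assumption throughout. The change should be made, but the concern does not undermine the design or call for more patients.

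**What to change.** 1. Record a session identifier for each intervention patient.
2. Before results are seen, prespecify a partially nested mixed model for the change in PedsQL score: a fixed effect for arm, a random session effect in the intervention arm only, and Satterthwaite or Kenward-Roger degrees of freedom. The degrees of freedom matter because 100 patients fill only about 13 to 20 sessions (100 / 8 to 100 / 5). State the assumed ICC.
3. Treat intervention patients who attend no session as single-person clusters, so that the intention-to-treat population is kept.
4. State a fallback: if the session variance is estimated at zero, which can happen with few small sessions, report the model without the session effect.
5. Make this the primary analysis. If the simple test stays primary, make it at minimum a prespecified sensitivity analysis.

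Adjusting the same model for baseline PedsQL score and age stratum does not address clustering. It is a separate gain in precision at no cost in data.

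The cost is one data field and a paragraph of analysis text; the model can be fitted in the SAS software already planned. The interval becomes slightly wider: with 80 evaluable per arm and SD 13.5, the half-width goes from 1.96 × 13.5 × √(2 / 80) = 4.18 points to 4.34-4.46 at ICC 0.05 (m = 4 to 6.4). Power falls by about 2 to 4 points at that ICC, before any further small loss from the reduced degrees of freedom.
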